### Randomization allocation

All PCP recruited to the study will be randomized into the intervention and control arms by the study statistician using standard randomization techniques. It is not necessary to randomized the the patients.

### Allocation concealment

It will not be possible to mask the study team to the status of the PCP, as they will be aware of the PCP participants in the training intervention arm. The study psychiatrist will be blinded/masked to the randomization status of the PCP, and therefore be unbiased with regard to the patients originating from each PCP (that is, whether a patient was diagnosed by a trained or untrained PCP). The study psychiatrist will therefore not be involved in the training program. In addition, patients will also be blinded to the PCP randomization status.

### Minimization of contamination

The PCP will be working in close, possibly overlapping geographical locations, thus there is a theoretical possibility of contamination by recruits having personal knowledge of each other. Additionally, there is a possibility of PCP in different study groups exchanging information received in the training. While we acknowledge that such interaction may potentially lead to contamination, it should be noted that this will be extremely difficult to prevent, and is not likely have a significant influence on the outcome. Because the training provided during the study is very thorough, and the study group participants are required to carry out intensive tasks, contamination through exchanges of information in informal discussions is not anticipated. However, as a preventive action, both the study and control group PCPs will be requested to refrain from seeking study-related information from each other for the duration of the intervention. At all possible times during recruitment, training, and monitoring, steps will be taken to observe potential contamination. At the end of the study, information will be gathered separately from both groups in order to gain an insight into potential contamination. However, it must be mentioned that, as this is a feasibility pilot study, minor contamination may not affect the outcomes to a large degree.

### Measurements

A sociodemographic questionnaire will be administered to all PCP, and this will include a section on medical education and experience at the point of recruitment. At baseline, PCP will also be given knowledge assessment questionnaires on each module included in the intervention training, to measure their existing knowledge. This will be repeated for the intervention arm during the training program at the start of each module. The knowledge-assessment questions to be used have been designed by the WHO to match the mhGAP training package. The same measure will be given to the control arm (without the training) at the same timepoint as the intervention arm. Post-training knowledge assessments (designed by the WHO) will be administered to the intervention arm at the end of the 5 day training program, and to the control arm at the same time. For both arms, knowledge assessment will be repeated at the end of the study period.

All patients who consent to participate will be given a sociodemographic questionnaire. At the point of recruitment, they will also be given an appropriate language version of the Patient Health Questionnaire (PHQ) as a screening measure [25]. The PHQ has been translated and used in both Sinhala and Tamil languages in the Sri Lankan IDP population [18]. The final instrument administered to patients will be the Sri Lankan version of the Client Service Receipt Inventory (CSRI) [26-28] to record health service utilization, including time lost from work. Both PHQ and CSRI will be administered at the point of recruitment and after the 3 month follow-up period.

### Primary outcomes and statistical analysis

Referral rates before and after the intervention will be measured for all PCP. Rates of study psychiatrist-verified diagnoses will be measured. Quality of adherence to mhGAP guidelines for treatment and management will be assessed for the intervention arm. Knowledge levels at the three test points will be measured for all PCP. For PCP in the intervention arm, knowledge levels will be assessed during each day of the training program. Overall comparisons will be made between the intervention and control arm rates for referral, correct diagnosis, and knowledge increase. Secondary outcomes include concurrence between the clinical diagnosis and the screening instrument and basic economic evaluation (described later).

No interim analysis will be carried out, and analysis will commence only at the end of the full study period. Because this is a pilot study, the analysis will be focused on primary feasibility, and therefore will primarily be descriptive in nature, with estimations of confidence intervals as appropriate [24]. As power calculations will not be carried out, it would not be appropriate to conduct analyses aimed at testing hypotheses [24]. The main analysis will be based on difference in outcomes of intervention and control arms using two-way analysis of variance (ANOVA). Appropriate consideration will be given to potential confounders. Results will be used to formulate sample size calculation for a larger intervention.

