**Methods/Design:**

This pilot randomized controlled trial will recruit 86 primary care practitioners (PCP) serving in the Puttalam and Mannar districts of Sri Lanka (with displaced and returning conflict-affected populations). The intervention arm will receive a structured training program based on the mhGAP intervention guide. Primary outcomes will be rates of correct identification, adequate management based on set criteria, and correct referrals of common mental disorders. A qualitative study exploring the attitudes, views, and perspectives of PCP on integrating mental health and primary care will be nested within the pilot study. An economic evaluation will be carried out by gathering service utilization information.

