Against this background, the proposed pilot study titled "An intervention to improve mental health care for conflict-affected forced migrants in low-resource primary care settings: a WHO MhGAP-based pilot study in Sri Lanka (COM-GAP)" aims to integrate mental health care into primary care by providing training to primary care practitioners (PCP) serving populations of IDP to improve identification, treatment, and referral of patients with CMD via the WHO Mental Health Gap Action Programme (mhGAP). The mhGAP initiative, introduced in 2008 by the WHO, incorporates evidence-based guidelines on managing mental, neurological, and substance abuse disorders in the primary care setting by non-specialist healthcare workers [7,22]. The mhGAP Intervention Guide (mhGAP IG), introduced in 2010, is a valuable manual that can be used as a resource in training non-specialists in primary mental health care, and is currently in its evaluation and implementation stage in several countries [7,8].

The primary objective of the proposed study is to assess the feasibility of improving/increasing identification, treatment, and referral of CMD by PCP working with a group of displaced and returning forced migrants in a resource-poor, rural, primary care setting via a training program based on the WHO mhGAP IG. This will be carried out by developing a pilot randomized controlled trial (ACT) in the north and north-western provinces of Sri Lanka. The main hypothesis of the study is that training intervention using mhGAP IG will increase rates of correct identification, treatment, and specialist referral rates of the PCP. It is envisaged that training PCP to efficiently identify, treat, and refer patients with CMD will reduce the acute and long-term disease burden, reduce service-provision costs, and provide effective/accessible mental health care to vulnerable/traumatized IDP. As South Asia faces continuous problems relating to mass forced migration, this study may provide important evidence on reducing the treatment gap for vulnerable populations in the region, with a high potential for scaling up in other resource-poor settings. This is the first study of its kind to be undertaken in Sri Lanka, and is planned as a local demonstration study to aid a future larger-scale intervention.

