During the first and second 3-month monitoring periods, the study coordinator will gather a list of patients diagnosed by the participant PCP (from both intervention and control arms) on a daily and weekly basis. These patients will then be approached individually by the study coordinator, who will explain the purpose of the study. The coordinator will provide an information leaflet and obtain secondary written consent from each patient. Consenting patients will then be directed to the study psychiatrist, who will reassess them according to mhGAP-based criteria for concurrence with the initial PCP diagnosis. Unless absolutely necessary, the psychiatrist will not modify or change the treatment or management outlined by the PCP. For those patients categorized as referrals to specialist care, their treatment and management will be provided by the study psychiatrist. However, referral patients will be completely free to decide if they want to be treated by the study psychiatrist or to seek care from other government or private specialist psychiatrists. All patients consenting to be involved in the study will be compensated for travelling costs or provided with travel if they prefer. No other compensation will be offered. For COM-GAP study phases according to CONSORT guidelines, please see the Additional file 1.

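### The abstract makes correct referrals a primary outcome, but the outcomes section measures unqualified referral rates and no stated assessment judges the referral decision

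*Protocol article*

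**What the plan says.** The protocol article describes the referral outcome in three places and the psychiatrist's assessment in a fourth.

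- **Abstract, Methods/Design:** "Primary outcomes will be rates of correct identification, adequate management based on set criteria, and correct referrals of common mental disorders". Referral carries a quality qualifier here.
- **Background, main hypothesis:** "training intervention using mhGAP IG will increase rates of correct identification, treatment, and specialist referral rates of the PCP". Correct stands before identification; whether it also governs referral is unclear.
- **Primary outcomes and statistical analysis:** "Referral rates before and after the intervention will be measured for all PCP", and later "Overall comparisons will be made between the intervention and control arm rates for referral, correct diagnosis, and knowledge increase". Here the qualifier belongs to diagnosis and not to referral.
- **Intervention:** consenting patients go to the study psychiatrist, "who will reassess them according to mhGAP-based criteria for concurrence with the initial PCP diagnosis". On referred patients the section says: "For those patients categorized as referrals to specialist care, their treatment and management will be provided by the study psychiatrist". That describes who gives care, not a rating of whether the referral was appropriate.

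The outcomes section also plans an assessment of adherence to the mhGAP guidelines, but for the intervention arm only. It adds that the results will be used to calculate the sample size of a larger intervention study.

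**The concern.** A count of referrals and a judgement of referrals are different variables. The first needs only the practitioner's action. The second needs an independent view of whether specialist care was indicated, for patients who were referred and for those who were not. The abstract promises the second and the outcomes section collects the first.

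Two things are at stake. A reader of the results could not tell whether the reported referral outcome is the one announced. And if the larger trial is to be about correct referral, raw referral rates from the pilot are the wrong input for its sample size.

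**Working it through.** **Step 1. Compare the definitions.** The abstract has correct referral. The outcomes section has referral rate, before and after, and a between-arm comparison of that rate. The hypothesis can be read either way. The definitions do not agree.

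**Step 2. Look for a measurement that could supply the abstract's outcome.**
- The psychiatrist's reassessment is tied to agreement on diagnosis. A correctly diagnosed patient may or may not need a specialist, so a verified diagnosis does not settle whether the referral was right.
- The adherence assessment might touch on referral, but it covers one arm and cannot give a comparison between arms.
- The Ethical issues section has the psychiatrist advise practitioners on significant errors. That is a safety step, not an outcome.

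No stated assessment yields correct referrals in both arms.

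**Step 3. Check whether the raw rate could stand in.** The documents give no referral figures, so all inputs here are assumed. Let *p* be the share of diagnosed patients who need referral, *s* the share of those who are referred, and *f* the share of the others who are referred.

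- Raw referral rate = *p·s* + (1 − *p*)·*f*
- Share of referrals that are correct = *p·s* / raw rate
- Share of decisions that are correct = *p·s* + (1 − *p*)·(1 − *f*)

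With *p* = 0.20:

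| Case | *s* | *f* | Raw rate | Referrals correct | Decisions correct |
|---|---|---|---|---|---|
| a | 0.50 | 0.1875 | 0.10 + 0.15 = 25% | 0.10/0.25 = 40% | 0.10 + 0.65 = 75% |
| b | 0.90 | 0.0875 | 0.18 + 0.07 = 25% | 0.18/0.25 = 72% | 0.18 + 0.73 = 91% |
| c | 0.50 | 0.30 | 0.10 + 0.24 = 34% | 0.10/0.34 = 29% | 0.10 + 0.56 = 66% |
| d | 0.80 | 0.05 | 0.16 + 0.04 = 20% | 0.16/0.20 = 80% | 0.16 + 0.76 = 92% |

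From a to b the raw rate is flat and referral improves. From a to c the raw rate rises and referral worsens. From a to d the raw rate falls and referral improves.

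**Step 4. Vary the assumption.** If the raw rate does not move, then *p*·Δ*s* = −(1 − *p*)·Δ*f*, and the change in correct decisions is *p*·Δ*s* − (1 − *p*)·Δ*f* = 2·*p*·Δ*s*. For a gain in *s* of 40 points:
- *p* = 0.20: 2 × 0.20 × 0.40 = 16 points (75% to 91%, as in a and b).
- *p* = 0.30: 2 × 0.30 × 0.40 = 24 points. For example, *s* goes from 0.30 to 0.70 and *f* from 0.30 to 0.1286; the raw rate is 30% both times, and correct decisions go from 58% to 82%.

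These cases are built to hold the raw rate still. They show what a raw rate can hide, not what it will hide.

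**The case against.** The case on the other side has four parts.

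**An increase has a stated rationale.** The Background lists low referral to specialist care among the known problems of common mental disorders in primary care, and nowhere describes over-referral. This stands. A reader might infer that the raw rate has no meaningful direction, or that the plan would reward over-referral; the documents support neither. The first overlooks that rationale. The second needs a success criterion, which the article does not set, and a firm reading of a hypothesis whose wording is ambiguous. What remains is that more referrals are not necessarily more correct referrals, and correct referrals are what the abstract names.

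**It is a feasibility pilot.** The analysis is to be mainly descriptive, hypothesis tests are said to be inappropriate, and referral is one of several measures. This also stands and limits the harm: no efficacy conclusion rests on the referral rate alone. It does not remove the effect on planning the larger trial.

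**An article condenses.** Criteria for a correct referral, its denominator and the rating form may be in the full protocol, and their absence from the article is not the fault raised here. But condensing does not explain why the abstract and the outcomes section name different quantities.

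**The illustration is constructed.** True. The 16- and 24-point gaps follow from assumed inputs chosen to keep the raw rate constant, and they presuppose diagnosed patients as the denominator, which the outcomes section does not state. They should not be read as expected effects.

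**Conclusion.** The inconsistency is real and concerns a primary outcome. The abstract states correct referrals; the outcomes section measures and compares unqualified referral rates; the only stated check by the psychiatrist is on diagnosis. Followed as written, the outcomes section would not deliver the abstract's outcome, nor the right event rates for a larger trial of correct referral.

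The raw rate is an imperfect proxy, not a meaningless one. That it can diverge from correct referral in either direction follows from the formulas; how far it would do so in this trial cannot be known from the documents. Because the pilot is descriptive and sets no success criterion, the consequence is a mislabelled outcome and a weak planning input, not an invalid trial.

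**What to change.** Use one definition of the referral outcome in the abstract, the hypothesis and the outcomes section. If correct referral is meant:

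1. The masked study psychiatrist records for each consenting diagnosed patient, in both arms and both monitoring periods, whether specialist referral was indicated, against pre-set mhGAP-based criteria. The content of those criteria is for the sponsor to set.
2. This is recorded before the practitioner's referral decision is disclosed. The order matters because the same psychiatrist goes on to treat referred patients and so must learn the decision.
3. Report by arm and period the proportion with an indicated referral who were referred, and the proportion without one who were not.
4. Keep the raw referral rate per practitioner as a descriptive measure.

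The cost is agreed criteria, one more form item and a sequencing step. No extra visits are needed, since these patients already go to the psychiatrist.

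Three limits should be stated:
- The measure covers only patients whom a practitioner diagnosed and who consented at both stages. Missed referrals among undiagnosed patients stay unmeasured.
- Training may change who is diagnosed, so the denominator may differ by arm.
- The Trial status section says the study has commenced. Patients already assessed may lack the item, and their number should be reported.

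### Adequate management is named a primary outcome, but the only management measure is taken in the intervention arm, and management is missing from the listed between-arm comparisons

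*Protocol article*

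**What the plan says.** The abstract (Methods/Design) states: "Primary outcomes will be rates of correct identification, adequate management based on set criteria, and correct referrals of common mental disorders". The last paragraph of the Background gives the main hypothesis, that "training intervention using mhGAP IG will increase rates of correct identification, treatment, and specialist referral rates of the PCP". Treatment or management is therefore one of three declared primary outcomes and one of three parts of the hypothesis.

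The section Primary outcomes and statistical analysis then treats the outcomes differently. For referral: "Referral rates before and after the intervention will be measured for all PCP". Knowledge is likewise measured in all practitioners. For management: "Quality of adherence to mhGAP guidelines for treatment and management will be assessed for the intervention arm". The comparison sentence reads: "Overall comparisons will be made between the intervention and control arm rates for referral, correct diagnosis, and knowledge increase". The main analysis is a two-way ANOVA of the difference between arms, and the results are to feed the sample size calculation for a larger study.

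Three other sections bear on whether a control rating is possible:

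- Intervention: control practitioners carry on with their existing practice, so they do manage patients. The study psychiatrist reassesses consenting patients from both arms, in both monitoring periods, for agreement with the diagnosis.
- Ethical issues: the psychiatrist is expected to be able to notice significant errors in the practitioners' management.
- Allocation concealment: "The study psychiatrist will be blinded/masked to the randomization status of the PCP".

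**The concern.** A primary outcome of a randomised comparison needs a value in each arm. Here the text attaches the management measure to one arm, and the list of comparisons is consistent with that restriction. Followed literally, the plan yields a description of management by trained practitioners and nothing to set it against.

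That leaves one part of the main hypothesis unaddressed. A one-arm rate cannot separate an effect of training from ordinary practice or from change over time. It also leaves the planners of the larger trial without a control rate or a difference for this outcome. Because the trial has commenced, control-arm management that goes unrated may not be recoverable later.

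**Working it through.** The point is structural, so the main check is to set the outcomes side by side, taking each row from the abstract and from Primary outcomes and statistical analysis.

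| Outcome | Primary in the abstract | Measured in | Listed for between-arm comparison |
|---|---|---|---|
| Correct identification | Yes | Psychiatrist-verified diagnoses (arm not restricted) | Yes |
| Referral | Yes | All practitioners, before and after | Yes |
| Adequate management | Yes | Adherence to the mhGAP guide, intervention arm | No |
| Knowledge | No | All practitioners | Yes |

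Management is the only abstract-level primary outcome tied to one arm and the only one absent from the comparisons. There are two ways to read the adherence sentence:

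1. Adherence is how adequate management is measured. The control arm then has no value, and the difference (intervention rate minus control rate) cannot be estimated, whatever the sample size.
2. Adherence is training fidelity, distinct from adequate management. The primary outcome then has no stated measurement and no listed comparison.

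Both readings leave the abstract and the Background unreconciled with the analysis section.

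Sample size: 2 × 43 = 86 agrees with the Sampling section. The 43 per arm cannot be re-derived, because no error rate, power, effect size or dropout rate is given. The point does not depend on it.

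To show what a two-arm rating would offer, I assumed one binary rating per practitioner, the same rate p in both arms, p from 0.2 to 0.5, and a normal approximation. The documents give no management rate.

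- One arm: half-width = 1.96 × √[p(1 − p)/n]
- Difference: half-width = 1.96 × √[2p(1 − p)/n]

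| n per arm | p | One arm | Difference |
|---|---|---|---|
| 43 | 0.2 | 0.120 | 0.169 |
| 43 | 0.3 | 0.137 | 0.194 |
| 43 | 0.5 | 0.149 | 0.211 |
| 34 | 0.2 | 0.134 | 0.190 |
| 34 | 0.3 | 0.154 | 0.218 |
| 34 | 0.5 | 0.168 | 0.238 |

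The rows with 34 per arm assume a dropout of about 20% (9/43 = 21%). As written, only the one-arm column is obtainable.

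**The case against.** The strongest reply is that two measures are being conflated. Only the intervention arm is asked to use the mhGAP guide, so adherence to it reads naturally as fidelity, which is properly assessed in the trained arm. The criteria for adequate management may sit in the full protocol, which is not shown. The fidelity reading is plausible, but it does not remove the problem. The comparison sentence names what will be compared and omits management, and the contrast between all practitioners for referral and one arm for management is stated in the text. This is not silence left by condensing.

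A second reply is that this is a feasibility pilot with descriptive analysis: "As power calculations will not be carried out, it would not be appropriate to conduct analyses aimed at testing hypotheses". That lowers the stakes, since no confirmatory claim depends on management. However, the plan still bases its main analysis on differences between arms, allows for confidence intervals, and intends to size a larger trial. For management, each of these needs control data.

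A third reply concerns the remedy. Patients are seen only if their practitioner diagnoses a common mental disorder and they consent, and training is meant to change whom practitioners diagnose. A two-arm management rate is therefore conditional on events after randomisation. This stands and belongs in the report as a caveat.

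A reader might also infer that rating one arm breaks the psychiatrist's blind. The documents do not support that. No adherence rater is named, the psychiatrist's stated task is agreement with the diagnosis, and ratings could be made blind for all patients or by staff who already know allocation. The risk arises only if the psychiatrist is asked to rate intervention-arm patients alone.

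**Conclusion.** The inconsistency holds. One of three declared primary outcomes, and one part of the main hypothesis, has no between-arm contrast under the plan as written; on the fidelity reading it has no stated measurement either. This rests on the text alone and on no assumed rate.

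Rated in both arms, the outcome could be estimated with a half-width of about 17 to 21 points at 43 per arm, or 19 to 24 points at 34. These figures depend on the assumptions above. Several patients per practitioner, or practitioners with no rated patient, would change them.

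A reader might try to put a size on the missing contrast. With an assumed 60% in the trained arm, for example, the difference could lie anywhere from 60 − 0 = +60 to 60 − 100 = −40 points. That range follows from any unmeasured comparator and says nothing about this trial, so it should not be quoted as a magnitude. Nor does the text show that the diagnosis outcome is biased through unblinding; that remains conditional on who rates adherence.

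**What to change.** In Primary outcomes and statistical analysis:

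- Have the blinded study psychiatrist rate management of every reassessed patient in both arms on the same pre-set criteria, using a form that does not record arm. Cover both monitoring periods as far as still obtainable, given that the trial has commenced.
- Add management to the between-arm comparisons, reported descriptively with a confidence interval and the caveat that it is conditional on practitioner diagnosis and patient consent.
- Report fidelity to the mhGAP guide in the trained arm separately, as a process measure. Name its rater, and arrange the rating so that it does not disclose arm to the study psychiatrist.

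If control-arm rating is not feasible, remove management from the primary outcomes in the abstract and from the hypothesis in the Background, so that the sections agree.

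The cost is revised wording, one form, and a short extra rating per patient at a reassessment already planned. No new patient contact is needed. Ratings for a period already completed may be lost.

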### Intervention

The training intervention will be based on the mhGAP IG developed by the WHO. Only relevant modules (depression, medically unexplained symptoms, alcohol abuse, and suicide) will be used for the training. The training will be based on a complete training guide and material provided by the WHO, which contains the necessary course material for trainees and preparatory and guidance materials for trainers. It will be conducted by the PI (who has been trained by the Royal College of Psychiatrists affiliated mhGAP training programme, UK), mhGAP IG experts, and another clinically experienced psychiatrist. Training programs will be conducted as a full-day course for five consecutive days, as originally designed by the WHO. The training intervention will be given to 43 (approximately half) of the recruited PCP in the intervention arm, randomized by appropriate techniques. Participants in the control arm will be given a similar training in mhGAP after the completion of the study.

Training will take place after an initial 3 month monitoring period of the whole sample from the date of recruitment (90 day monitoring period for each participant from the date of recruitment). During this period, all PCP are required to inform the study coordinator immediately on diagnosing a primary care patient with CMD. The PCP is required to obtain written informed consent from each patient if they agree to be contacted by the research team, prior to informing the coordinator. All PCP will be given initial training on ethics and informed consent procedures prior to commencing the study.

After the 5 day training period of the intervention group, both arms will be monitored again for a 3 month period. Those in the intervention arm will be required to use the mhGAP guide to diagnose, treat, and refer patients with possible mental health problems whom they encounter in their respective primary care settings. The control arm will be requested to continue their existing diagnostic and treatment practices. Participants in both arms will be required to communicate any CMD diagnoses to the study coordinator immediately.

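### The main analysis is a two-way ANOVA with unnamed factors, set right after hypothesis testing is disclaimed, with no term for repeated measurement of the same practitioner; a baseline-adjusted estimate would be clearer and more precise

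*Protocol article*

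**What the plan says.** All points below are from the protocol article.

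- *Primary outcomes and statistical analysis* says the analysis "will primarily be descriptive in nature, with estimations of confidence intervals as appropriate". It continues: "As power calculations will not be carried out, it would not be appropriate to conduct analyses aimed at testing hypotheses".
- The next sentence reads: "The main analysis will be based on difference in outcomes of intervention and control arms using two-way analysis of variance (ANOVA"). It names neither the two factors, nor the unit of analysis, nor the term that will be read as the result.
- *Background* nevertheless states a directional hypothesis: "The main hypothesis of the study is that training intervention using mhGAP IG will increase rates of correct identification, treatment, and specialist referral rates".
- The same practitioners are measured repeatedly. *Intervention* describes a 3-month monitoring period before training, after which "both arms will be monitored again for a 3 month period". *Primary outcomes and statistical analysis* adds: "Referral rates before and after the intervention will be measured for all PCP" and "Knowledge levels at the three test points will be measured for all PCP".
- *Randomization allocation* makes the PCP the randomised unit, and *Sampling* gives 43 per arm.
- The results are to inform the sample size of a larger study.

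**The concern.** There are two separate difficulties.

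The first is framing. An analysis that disclaims hypothesis testing is followed at once by a method usually reported as F-tests, and elsewhere there is a directional main hypothesis. A reader cannot tell whether the headline result will be an interval or a p-value.

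The second is the model. Each randomised PCP supplies a value before and a value after training. An ordinary two-way ANOVA with arm and period as factors treats these as independent observations. That misstates the standard errors, and in opposite directions for the two terms that might be read. The arm main effect has a further problem: it averages in the pre-training period, when training can have had no effect.

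At stake are the width and meaning of the intervals that form the pilot's between-arm result, and whether the pilot reports the quantities its successor needs (between-PCP SD, pre/post correlation).

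**Working it through.** **The plan's own figure.** 2 × 43 = 86, which agrees with *Sampling*. No alpha, power, effect size or drop-out rate is given, so 86 cannot be reproduced further. Nothing below bears on it.

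**Inputs.** n = 43 PCP per arm (*Sampling*). Assumed, because the document gives none: a continuous outcome with SD 1 in each arm and period, pre/post correlation r = 0.3, 0.5 or 0.7, and factors arm and period. Drop-out is ignored; a smaller n widens every half-width by the same factor and leaves the ratios unchanged.

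**Arm-by-period term (difference in change).**
- SE from the ordinary ANOVA: √(4/n) = √(4/43) = 0.305. Half-width 1.96 × 0.305 = 0.60, whatever r is.
- Correct SE, which a paired (mixed) ANOVA would use: √(4(1−r)/n).
- SE of the post-training difference adjusted for baseline (ANCOVA): √(2(1−r²)/n).

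| r | ordinary half-width | correct (paired) SE; half-width | ANCOVA SE; half-width | actual type I error, ordinary |
|---|---|---|---|---|
| 0.3 | 0.60 | 0.255; 0.50 | 0.206; 0.40 | 0.019 |
| 0.5 | 0.60 | 0.216; 0.42 | 0.187; 0.37 | 0.006 |
| 0.7 | 0.60 | 0.167; 0.33 | 0.154; 0.30 | 0.0003 |

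The ordinary SE is 1.20, 1.41 and 1.83 times too large. A simulation of 20,000 trials per correlation gave type I errors of 0.020, 0.006 and 0.0003.

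**Arm main effect.**
- Dilution: the term averages the two periods. A true post-training effect of 0.50 SD is estimated as (0 + 0.50)/2 = 0.25 SD.
- Ordinary SE √(1/n) = 0.152; correct SE √((1+r)/n) = 0.174, 0.187 and 0.199.
- Actual type I error 2(1 − Φ(1.96/√(1+r))) = 0.086, 0.110 and 0.133 (simulation 0.085, 0.109, 0.130).

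**Baseline adjustment against a correctly paired ANOVA.** The half-width ratio is √((1+r)/2) = 0.806, 0.866 and 0.922, so ANCOVA is 19%, 13% and 8% narrower at r = 0.3, 0.5 and 0.7. This gain remains even under the most favourable reading of the sentence.

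**The case against.** The strongest reply is that the model criticised is assumed. The article names no factors, and a two-way mixed ANOVA fits the wording and would handle the pairing. An analysis plan that is not shown may say so. This stands: the 0.60 half-width and the type I errors apply only to an ordinary arm-by-period model. The halving applies only if the arm main effect is the reported term, whereas measuring referral before and after training points rather to the interaction. The two errors would not both affect one estimate.

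Four stronger conclusions might be inferred, and the document does not support them.

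- *That ANOVA cannot yield estimates.* It is a linear model and gives mean differences with intervals. The clash with the no-testing statement is one of framing, and wording can cure it.
- *That the variances passed to the larger study would be wrong.* Even in the ordinary arm-by-period model with equal variances, the within-cell mean square is unbiased for the single-period variance and the interaction contrast is unbiased for the training effect. It is the standard errors that are wrong.
- *That clustering of patients within PCP is the central flaw.* With one rate per PCP and period, aggregation largely absorbs it, leaving unequal denominators and possibly PCPs with no diagnosed patients. It matters if patients are the unit: with an assumed 5 to 10 patients per PCP and ICC 0.05 to 0.10, the design effect 1 + (m−1)ICC is 1.20 to 1.90 and the actual alpha 0.07 to 0.16.
- *That the ordinary interval's full excess over ANCOVA is error.* At r = 0.5, 0.60/0.37 is about 1.6, but only 0.60/0.42 = 1.41 comes from ignoring the pairing. The rest is the efficiency gain from baseline adjustment.

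Finally, this is a self-declared feasibility pilot with a mainly descriptive analysis and no decision rule tied to the ANOVA, which limits the harm.

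**Conclusion.** The point holds in a conditional form. The protocol fixes an under-specified two-way ANOVA as its main analysis, immediately after disclaiming hypothesis tests, and provides no term for repeated measurement of the randomised practitioner. This is more than missing detail, because the named method is dominated by a simple alternative. If it is run as an ordinary arm-by-period ANOVA, the half-width is 0.60 SD where 0.50 to 0.33 is correct. If it is run as a paired ANOVA, the standard error is right but the interval is still wider than the baseline-adjusted 0.40 to 0.30.

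The figures rest on assumed correlations of 0.3 to 0.7 and a unit-SD continuous outcome. They are indicative for the rates, whose denominators will vary between practitioners. The document does not establish that the ordinary model is intended or that the arm main effect would be reported. The finding is an improvement available at almost no cost, not a defect that invalidates the pilot.

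**What to change.** Replace the ANOVA sentence with the following content.

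1. For each between-arm outcome, the estimate is the PCP-level difference between arms in the post-training period with its 95% CI. It is adjusted for the PCP's own value in the first 3-month period (referral and verified-diagnosis rates) or at the baseline test (knowledge score).
2. Use ANCOVA or, for proportions among diagnosed patients, a binomial GEE or mixed model with PCP as the cluster. State how a PCP with no diagnosed patients in a period is handled.
3. State that estimates and intervals, not p-values, are the result.
4. Report the PCP-level SD, the pre/post correlation and, where patients are modelled, the ICC, for sizing the larger study.

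Two limits follow from the data described. Do not use consultation counts as an offset unless they are recorded; the article mentions only patients diagnosed with common mental disorders. Do not compare management adherence between arms, since it is to be assessed in the intervention arm only.

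The cost is wording. The baseline monitoring period and baseline knowledge test are already planned, and no extra participants or visits are needed. The trial has commenced, but analysis is to start only when the study period ends, so the change should be dated and made before then.
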